### Cultural safety and data collection procedures

We are mindful that ageing and life-transitions are sensitive topics and, thus, utilised our prior experience to protect kaumātua participant confidentiality and provide cultural safety. To this end, we developed a detailed health and safety plan at the beginning of the project, working with both advisory groups, for the intervention orientation and data collection to ensure cultural safety for participants. The research procedures were approved by the University of Waikato Human Research Ethics Committee through the Faculty of Māori and Indigenous Studies.

The participants will be able to complete the questions on their own or via a structured interview and have a support person present if they desire. The questionnaire includes both English and Māori language versions. The Māori language version was developed through a translation and back-translation procedure to establish equivalence. Finally, the questionnaire is written with large font and with plenty of spacing between questions to support kaumātua in reading the content.

### Data analysis plan

#### Pre-test data

Using the pre-test data, we will (re-)establish the psychometric properties of measures. Factorial and discriminant validity will be assessed with confirmatory factor analysis (CFA) and reliability established with Cronbach’s alpha. Fit indices will include χ^2^/degrees of freedom (χ^2^/df), comparative fit index (CFI), Tucker-Lewis index (TLI), and standardized root mean square residual (SRMR). Good fit was determined if CFI and TLI were at or above .90 with .95 as ideal, SRMR was less than .08 with .06 as ideal, and χ^2^/df < 3 or less than 2 as ideal [71]. Analysis will be completed with AMOS 25.0. We will confirm specific measures and also consider high-order factor models of mana motuhake and hauora. Convergent validity will be established using Pearson correlations among the measures (using SPSS 25.0).

Multivariate models of several dependent variables (i.e., HRQOL, perceived autonomy, loneliness, and sense of purpose) will be constructed using hierarchical regression. Variables will be entered in two blocks: demographics and other variables. We will simplify the models by removing variables not significant at a .10 level. Data analysis will be completed with SPSS 25.0.

We will analyse the qualitative data using thematic analysis [72, 73]. All responses will be transcribed prior to analysis. Themes will be identified using three criteria: recurrence, repetition, and forcefulness [74]. All analyses will be completed by at least two researchers—at least one of whom will be Māori. Specifically, the process will include reading of responses and identifying initial codes. Themes will have to be agreed upon by both researchers for inclusion. Discussion among the coders will be used to clarify and develop themes. The final themes will be reviewed by the research team and advisory boards and shared with participants for validation. Themes will also be compared across the three time periods to explore potential patterns.

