### Study design

The research design for the evaluation of the orientation programme is a pre- and post-test, clustered staggered design with T1 (target *n* = 15) and T2 (target *n* = 15) groups. T1 will participate in the orientation programme initially, while T2 will participate in a subsequent orientation. The peer educator capacity of tuakana will be assessed at three stages: pre-intervention, post-intervention for the T1 group, and post-intervention of the T2 group. After the orientation programme, each tuakana will talk with each teina at least three times to address the specific life-transitions of teina. Teina also will complete three evaluations with variations for the two groups: (a) T1: pre-intervention, approximately four months post-intervention, and then four months after the second evaluation; (b) T2: pre-intervention, approximately four months after initial survey, and then four months post-intervention. This staggered approach was approved by the Board Advisory Group during the original proposal as fitting the mission of the organisation and the needs of kaumātua. Consistent with Kaupapa Māori principles, withholding an intervention from participants is not ethical. Thus, the research design enables a rigorous comparison of the orientation programme whilst ensuring that all teina receive the intervention. Further, the use of a staggered design is a strong, and pragmatic design for interventions in the health service sector [56]. Figure 1 illustrates the staggered research design. The project is registered with the Australia New Zealand Clinical Trial Registry (ACTRN12617001396314).

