### Measures

The measures included in this study centre on two core constructs: hauora (health) and mana motuhake (see Table 1 for a summary). Hauora is conceptualised using the whare tapa wha (four walls of a meeting house) model of health and wellbeing developed for Māori communities [59]. The model includes tinana (physical/body), hinengaro (mind/thought/intellect), whanaungatanga (social) and wairua (spiritual). Hauora is a necessary (although not sufficient) condition for achieving mana motuhake. Measures of these two supra-constructs include both quantitative and qualitative questions and will be part of both tuakana and teina surveys across the three-time periods. We will include demographic questions only at pre-intervention (e.g., ethnicity, age, relationship status, care of grandchildren, and who else lives with them). We also will include additional measures related to the intervention. The total number of questions were limited and short measures were used in awareness of response burden for kaumātaua.

**Table 1 Tab1:** Constructs and Measures

Construct	Measures	Number of Items
*Pre- and Post-Test Measures*		
Hauora—tinana/hinengaro	Self-rated health	1
Hauora—tinana/hinengaro	Health related quality of life—physical and mental wellbeing	7
Hauora-hinengaro	Knowledge and likelihood of using services	3
Hauora-wairua	Spirituality	1
Hauora-whanaungatanga	Loneliness	4
Hauora-whanaungatanga	Cultural connection	4
Hauora-whanaungatanga	Social support	4
Hauora-whanaungatanga	Perceived burden & benefit	4
Mana motuhake	Economic wellbeing	3
Mana motuhake	Perceived autonomy	3
Mana motuhake	Global life satisfaction	1
Demographics	Living situation	3
*Intervention Measures*		
Mana motuhake	Satisfaction with interaction	3
Mana motuhake	Sense of purpose	3
Mana motuhake	Self-efficacy as a tuakana	5
Mana motuhake	Perceived effectiveness of orientation programme	4

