### Mana Motuhake

We will include three quantitative measures of mana motuhake and several open-ended questions for both tuakana and teina. Economic wellbeing focuses on needs related to paying bills, quality of housing, and control of resources. Two items come from Te Kupenga and one was created for this study [63]. Perceived autonomy examines the independence that kaumātaua self-reported and will be measured with two items from a previous study [66] and one item from Te Kupenga. Global life satisfaction will be measured using the Cantril ladder [67]. Finally, we will ask five open-ended questions about general life concerns, concerns in the next few years, best things in life, what would improve their lives and how they assess their own mana motuhake. For tuakana only, we also will ask questions about sense of purpose. Three self-reported items will be included based on a previous study [68].

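### Removing predictors at p ≥ .10 invalidates the inference from the pre-test regressions, most seriously for sense of purpose (at most 30 tuakana), and Table 1 conflicts with the text on when that measure is taken

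*Protocol article*

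**What the plan says.** The *Pre-test data* part of the Data analysis plan states: "Multivariate models of several dependent variables (i.e., HRQOL, perceived autonomy, loneliness, and sense of purpose) will be constructed using hierarchical regression". Variables go in as two blocks, demographics first and then the rest, followed by one rule for all four outcomes: "We will simplify the models by removing variables not significant at a .10 level". The number of candidate variables is not given, and the outcome with fewer respondents gets no separate handling.

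Under *Mana Motuhake*: "For tuakana only, we also will ask questions about sense of purpose". *Study design* fixes the number of tuakana through a "clustered staggered design with T1 (target *n* = 15) and T2 (target *n* = 15) groups".

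On timing, Table 1 has one block for pre- and post-test measures and another for intervention measures. The row "Sense of purpose" (three items) is in the second block. The *Measures* text says that measures of hauora and mana motuhake "will be part of both tuakana and teina surveys across the three-time periods". *Study design* adds: "The peer educator capacity of tuakana will be assessed at three stages: pre-intervention, post-intervention for the T1 group, and post-intervention of the T2 group".

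**The concern.** There are two separate issues.

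1. **Selection on p-values.** After variables are deleted because they missed a threshold, the software reports the survivors as if that model had been fixed in advance. Their p-values are too small, their intervals too narrow and R-squared too high. This applies to all four outcomes and worsens as respondents per candidate fall. Sense of purpose is the extreme case, yet it gets the same rule as outcomes asked of everyone. Readers could take the surviving variables as established correlates of purpose among peer educators.

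2. **Timing of the measure.** Objective (a) names sense of purpose as something the programme should improve in tuakana. If a data collector followed the Table 1 block literally, it would not be asked at pre-test. There would then be no pre-test regression and no baseline for change.

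The second issue does not cause the first. Small numbers and pruning cause the instability.

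**Working it through.** **Inputs from the article.** Tuakana: 15 + 15 = 30 (*Study design*). Teina: target 180 (*Sample and recruitment*), which is 30 × 6. Respondents for health-related quality of life, autonomy and loneliness: up to 180 + 30 = 210. Respondents for sense of purpose: at most 30. Removal threshold: .10.

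**The plan's own figure.** The only power figure is .80 for the teina comparison (d = .55, intra-class correlation .10, six teina per tuakana). The design effect is 1 + 5 × .10 = 1.5, giving 90/1.5 = 60 effective teina per group. Power is .79 to .85, depending on how d is standardised and whether a t or normal reference is used. The stated figure is reproduced, but it does not cover the 30-person regression, for which no precision is stated.

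**Assumed number of candidates.** Table 1 has 11 pre- and post-test constructs besides demographics, and *Measures* gives five example demographics: 11 + 5 = 16. Ethnicity will hardly vary (15), and the services questions are mostly open-ended (14). If investigators enter fewer, 8 to 12 is plausible. The range used is 8 to 16. At 15 candidates there are 30/15 = 2 tuakana per candidate, against 210/15 = 14 for the other outcomes.

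**Hand check, no true predictor.**
- Chance that one round of deletion keeps at least one of k independent null variables: 1 − 0.9^k. For k = 8 this is 57%; for k = 15 it is 79%.
- Expected R-squared of the full null model: k/(n − 1). At n = 30, 8/29 = .28 and 15/29 = .52. At n = 210, 15/209 = .07.

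**Simulation, no true predictor.** Backward elimination at .10, predictor correlation .3, 1,500 to 2,000 runs at n = 30 and 500 at n = 210:

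| n | Candidates | Mean noise variables kept | At least one kept | Mean apparent R-squared |
|---|---|---|---|---|
| 30 | 8 | 1.1 | 61% | .14 |
| 30 | 12 | 1.9 | 76% | .22 |
| 30 | 14 | 2.5 | 82% | .27 |
| 30 | 15 | 2.8 | 86% | .30 |
| 30 | 16 | 3.1 | 88% | .33 |
| 210 | 16 | 1.9 | 82% | .04 |

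With independent predictors and 15 candidates at n = 30 the results are 84% and .29. A separate run gave 57–62% with 8 candidates and 84–86% with 15, with at least one survivor at p < .05 in 39–45% and 73–74%.

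At n = 210 a spurious survivor is about as likely as at n = 30 with the same candidates, so the rule harms inference for all four outcomes. What changes with n is the inflation of R-squared.

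**Simulation with real signal.** Share of retained variables that are noise, at true R-squared .3 / .5:

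| n | Candidates | Three true predictors | Five true predictors |
|---|---|---|---|
| 30 | 8 | 36% / 27% | 21% / 17% |
| 30 | 12 | 54% / 44% | 44% / 36% |
| 30 | 15 | 65% / 55% | 55% / 48% |
| 30 | 16 | 68% / 59% | 58% / 51% |

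At n = 210 with three true predictors the share is 14–34%, and nearly all true predictors are kept. At n = 30 the power to retain a variable with partial correlation .3 is only 40% (8 candidates), 35% (12) or 29% (16), so real predictors are often lost as well.

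**Timing, side by side.** Table 1 puts sense of purpose in the same block as satisfaction with the interaction and perceived effectiveness of the orientation, neither of which can exist before the intervention. Against that, four places point to pre-test collection: the regression itself, which sits under *Pre-test data*; the description under *Mana Motuhake* rather than *Intervention-related measures*; the three-period sentence in *Measures*; and the pre-intervention assessment of tuakana in *Study design*. The table and the text cannot both be taken literally.

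**The case against.** **The candidate list is not fixed, and choosing it is usually left to an analysis plan.** This stands in part. Higher-order factor models are to be considered and could shorten the list. With about 8 candidates or strong signal, noise is a minority of what is kept. A reader might infer that the sense-of-purpose model will mostly report noise. That needs either no signal, or roughly 14 to 16 candidates with weak to moderate signal, and the article establishes neither. But the removal rule is a stated choice, not an omission, and even 8 null candidates leave a spurious survivor in about 60% of samples.

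**Three of the four outcomes have far more respondents.** This stands. A reader might infer that the published predictors will be largely chance findings throughout. With up to 210 respondents the null R-squared is only about .03 to .04, and true predictors are kept. For these outcomes the defect is invalid post-selection inference.

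**Nothing in the trial's main result depends on these models.** This stands. *Intervention evaluation* uses separate multilevel models, so the effect estimate, the power figure and the cost-effectiveness analysis are untouched.

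**The Table 1 point is only a sub-heading.** This stands in part. The table might be read as showing that there is no baseline for sense of purpose, but the other sections point the other way. It might also be read as requiring self-efficacy as a tuakana to move to the pre-test block. That is only inferred: Table 1 and *Intervention-related measures* agree on its place, and *Study design* does not define peer educator capacity as that scale.

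**Replacing the model with correlations does not remove chance findings.** This stands. Fifteen independent null tests give 1 − 0.95^15 = 54% with at least one p < .05. Correlations help only if reported as estimates with intervals and labelled exploratory.

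**Conclusion.** The point holds in a limited form. Deleting variables at .10 makes the p-values, intervals and R-squared of the reduced models invalid for all four pre-test outcomes. For sense of purpose, with at most 30 respondents, the model is unstable and overfitted, with a high chance of spurious predictors: with no true relation, about 60% of samples keep at least one variable with 8 candidates and about 85% with 15, at apparent R-squared about .13 and .30. These figures rest on an assumed 8 to 15 candidates, full recruitment of 30 tuakana, and repeated removal at .10; a single round gives 57% and 79%.

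The timing of sense of purpose is a genuine inconsistency that needs reconciling. It does not show that the baseline is missing.

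**What to change.** 1. Delete the .10 removal rule from *Pre-test data*.
2. For health-related quality of life, perceived autonomy and loneliness, name the variables in each block in advance and report the full two-block models with confidence intervals.
3. For sense of purpose, limit the model to a few pre-named predictors, or report correlations with intervals. Make no selection on p-values, and label the result exploratory.
4. Reconcile Table 1 with *Study design*, *Measures*, *Mana Motuhake* and *Pre-test data*, stating explicitly whether sense of purpose is asked of both tuakana groups at pre-test, so that the baseline for objective (a) is collected.

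The cost is a change of analysis wording and a table correction, with no extra participants. The reported models will be less parsimonious. If sense of purpose is not already in the pre-test questionnaire, three short items are added for 30 tuakana.

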#### Intervention evaluation

The purpose of the analysis is to determine whether the peer-educator model results in changes to hauora and mana motukahe between pre-test and post-test. The analysis will compare the two groups and identify if there are intervening variables that explain differential patterns in the changes in the dependent variables*.* The dependent variables are mana motuhake and haurora. The independent variables are the time receiving the orientation programme (T1/T2) and the three time periods (pre-intervention, post T1-intervention, post T2-intervention). Potential intervening variables that will be controlled for include characteristics about the conversations, characteristics of the tuakana/teina, and whether participants talked with each other during the intervention.

The quantitative data are at three levels—repeated measures of variables (three-time periods), individual characteristics of the teina/tuakana, and characteristics about the conversations with the tuakana. The inclusion of multiple levels requires the use of multilevel statistical models to account for clustering. The analysis will account for the nature of the change in the variables along with characteristics about the teina and tuakana that may influence those changes.

Further, we will determine estimates of cost effectiveness using incremental cost effectiveness analysis (ICEA) [75, 76]. Cost-effectiveness analysis involves estimating the cost per unit improvement in the primary outcome variable. We will use HRQOL as an outcome measure for the ICEA [77]. ICEA involves estimating the ratio of the increase in the outcome variable (as measured by the estimated effect size from the intervention trial) to the estimated average cost per participant of the programme (the incremental cost-effectiveness ratio, or ICER). This calculation assumes that the cost of the status quo (no intervention) is zero. ICER is a common measure used in the evaluation of cost-effectiveness of health interventions [78, 79]. The ICER can then be compared with an explicit target (or costs of alternatives) to determine cost effectiveness.

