### Sample and recruitment

Tuakana will be purposively sampled to include kaumātua with effective peer educator attributes. The advisory groups considered the relevant peer educator attributes for ageing research [41] and attributes within Te Ao Māori such as mana, pono, aroha and tika [6, 19]. Tuakana will receive koha (an offering) towards their participation in the programme, conversations with teina, and data collection over the duration of the project (approximately $45/event).

The project will have a target of 180 teina participants randomly selected from the RKCT client base of approximately 600 kaumātua that affiliate to various iwi (tribes). Tuakana will be removed from the sampling frame. Teina will be assigned to a tuakana with matched biological sex. The only exclusion criteria is ethnicity (i.e., not being Māori). Decline and retention rates (including reasons such as withdrawal and passing away) will be tracked. Teina will receive koha as a contribution towards their participation in conversations and data collection (approximately $40/event). Tuakana and teina will be assigned to T1 and T2 groups ideally using random assignment although convenience assignment will be accommodated and tracked (e.g., when they were able to participate or to match tuakana/teina).

The sample sizes of tuakana and teina were determined by a balance of resources and statistical power to determine the optimal design. We conducted power and sample size estimates based on the research design [57] and confirmed with the ‘od.exe’ software package [58]. The following assumptions were made: (a) probability value = .05; and (b) rho (intra-class correlation) = .10. Six teina for each tuakana results in power of .80 with a medium effect size (d = .55). A medium effect size was chosen given prior research on the impact of elder peer educators on self-rated health and related wellbeing outcomes [37, 38].

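### The pre-intervention score is modelled as an outcome occasion and not named as a covariate; conditioning on it would sharpen the T1 versus T2 comparison at almost no cost

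*Protocol article*

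**What the plan says.** All references are to the protocol article.

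- **Intervention evaluation.** The dependent variables are mana motuhake and hauora. The independent variables are "the time receiving the orientation programme (T1/T2) and the three time periods (pre-intervention, post T1-intervention, post T2-intervention". The three repeated measures form one level of a multilevel model. The section adds: "The analysis will account for the nature of the change in the variables along with characteristics about the teina and tuakana that may influence those" (the closing word, left out here, refers back to the change just mentioned). The controlled variables it names are features of the conversations, features of the tuakana and teina, and whether participants talked with each other. The participant's own pre-intervention score is not named.
- **Measures.** The hauora and mana motuhake measures "will be part of both tuakana and teina surveys across the three-time periods", so a baseline value on the same measure is collected.
- **Study design.** There are "T1 (target *n* = 15) and T2 (target *n* = 15) groups". At the second survey T1 has received the intervention and T2 has not. By the third survey both have.
- **Sample and recruitment.** "The project will have a target of 180 teina participants". The power assumptions are "probability value = .05" and "rho (intra-class correlation) = .10", with the result: "Six teina for each tuakana results in power of .80 with a medium effect size (d = .55"). No pre-post correlation is given. Assignment to T1 or T2 is random if possible, but convenience assignment is allowed and tracked.

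**The concern.** The second survey is the only point at which a treated group can be compared with a concurrent untreated one. How baseline enters the model decides how precisely that comparison is estimated.

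If the pre-test is an outcome occasion and the two groups' baseline means are left free, the contrast at the second survey equals T1's mean change minus T2's mean change. That estimator subtracts the whole baseline difference, whatever the correlation between occasions. With r below 1 this over-corrects a chance imbalance, which is plausible with 15 clusters per group, and it discards information already collected.

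The power statement lists alpha, ICC, cluster size and effect size only. It therefore fits a single post-test comparison, and it does not show how baseline is to be used.

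**Working it through.** **Inputs from the article.** 15 + 15 = 30 tuakana; 6 teina each, 180 in all; ICC .10; d = .55; alpha .05, taken as two-sided because the side is not stated. **Assumed:** r, the pre-post correlation of tuakana-cluster means, shown over a range.

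**Step 1: the plan's own figure.**
- Design effect = 1 + (6-1)(.10) = 1.5.
- Variance of the post-test difference = 4(1.5)/180 = .0333; SE = .1826.
- Noncentrality = .55/.1826 = 3.01; noncentral t with 28 df gives power **.83**.
- Five teina per tuakana give .785, so six is the smallest cluster size that reaches .80. The stated figure is reproduced as a post-test comparison that makes no use of baseline.

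**Step 2: two uses of baseline at the second survey.**
- Difference in change: multiply the variance by 2(1-r), 28 df.
- Baseline as covariate: multiply it by 1-r², 27 df.
- Ratio: (1-r²)/[2(1-r)] = (1+r)/2, which is below 1 for every r below 1. At r = .5 the variance falls by 25%.

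| assumed r | 2(1-r) | 1-r² | power, change | power, baseline-adjusted |
|---|---|---|---|---|
| .3 | 1.40 | .91 | .69 | .86 |
| .4 | 1.20 | .84 | .76 | .89 |
| .5 | 1.00 | .75 | .83 | .92 |
| .6 | .80 | .64 | .90 | .95 |
| .7 | .60 | .51 | .96 | .98 |

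**Step 3: where the change contrast crosses .80.** With 28 df, power is .80 when the effect is .530. The variance factor at d = .55 may therefore rise to (.55/.530)² = 1.077. Setting 2(1-r) = 1.077 gives r of about .46. Below that the second-survey change contrast has less than .80 power; above r = .5 it has more than the post-test comparison.

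**Step 4: adding the third survey.** Suppose the effect is coded by exposure, is sustained, and all occasions are equally correlated.
- Baseline means free: factor 1.5(1-r). At r = .3 this is 1.05, power .81. At r = .5 it is .75, power .92.
- Common baseline mean: factor (1-r)(1+2r)/(1+r). At r = .3 this is .7 × 1.6/1.3 = .86, power .88. At r = .5 it is .5 × 2/1.5 = .67, power .94 to .95 (27 or 28 df).

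The loss from leaving the baseline difference free is smaller here, but it does not vanish.

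**The case against.** **The change contrast is inferred.** The section writes out no group-by-period term, no constraint on baseline means and no named contrast. A model with a common baseline mean also has the pre-test as an outcome occasion, fits the same wording, and is about as efficient as covariate adjustment. Such detail may sit in an analysis plan that is not shown. This stands as a limit on certainty. Still, the text lists T1/T2 as a factor next to all three periods, frames the question as differential change, and leaves the own baseline score out of the named controls. The free-fit reading is the most natural one, though not the only one.

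**A reader might infer that the trial is underpowered.** The document does not support that. It would need r below about .46, a figure the article never gives, and a contrast that ignores the third survey. The dependent variables may be multi-item or higher-order scores, and the relevant r is that of tuakana-cluster means, so a low r cannot be presumed.

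**Convenience assignment.** Where groups are not formed at random, baseline adjustment and change scores can estimate different quantities, and neither is always less biased. This stands: the precision argument applies fully only to randomly assigned participants.

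**The planned model is valid.** Agreed. The point concerns efficiency; it is not an error that invalidates the comparison.

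**Conclusion.** The point holds as a cheap improvement. On the most natural reading, the planned T1 versus T2 contrast at the second survey is a difference in change. Under random assignment this is less precise than conditioning on the collected baseline for any r below 1. The gain in power is about 17 points at r = .3, 9 at r = .5 and 2 at r = .7. These sizes rest on the article's design inputs, a two-sided test, an assumed r, and a contrast at the second survey only. The gain is smaller if the third survey contributes: .81 versus .88 at r = .3. It is not shown that the stated .80 is missed.

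**What to change.** In the Intervention evaluation section, state that the T1 versus T2 effect at the post-baseline surveys is estimated with the participant's own pre-intervention score on the same measure as a covariate, keeping the tuakana clustering. Where assignment was random, a repeated-measures model with a common pre-intervention mean is an acceptable alternative. Because Sample and recruitment allows convenience assignment, report the unadjusted change contrast alongside it and say in advance that the two may differ in non-random groups.

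Cost: wording only, with no new data or participants. Missing pre-tests must be handled, by imputation or by the common-mean model where assignment was random, and two estimates must be shown and explained.
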